### Outcomes

#### Primary outcome

The primary efficacy endpoint is the change in the composite clinical motor score (CCMS) from baseline to week 12, assessed in the on-medication state. The CCMS is a validated composite index that integrates three key motor domains—bradykinesia (derived from MDS-UPDRS Part III, 40% weight), manual dexterity (from the Purdue Pegboard Test, 30% weight), and mobility (from the Timed Up and Go [TUG] Test, 30% weight)—to offer a sensitive, multidimensional evaluation of motor function. It is calculated as follows: [(MDS-UPDRS III − 23.8829) × 0.0377 + (−1 × Purdue Pegboard Test + 28.9286) × 0.0739 + (Timed Up and Go Test −9.8746) × 0.1414 + 3.8239] × 6.0946, providing a comprehensive assessment of motor function improvement, including bradykinesia, dexterity, and mobility (37). Developed and validated in the Oxford Discovery cohort of over 900 early-stage PD patients (37), CCMS outperforms MDS-UPDRS Part III alone, with a wider score distribution for subtle changes, a lower coefficient of variation (37% vs. 67%), and a stronger correlation with patient-reported motor severity (*r* = 0.65 vs. 0.61). Its enhanced longitudinal sensitivity in early-stage PD reduces sample size requirements by 64% in trial simulations, making it ideal for detecting acupuncture’s modest, clinically meaningful effects that conventional scales might overlook. Additionally, participants will undergo assessment in the off-medication state (after a 12-h withdrawal from antiparkinsonian medication) at week 12 to evaluate the independent effects of acupuncture on motor function.

#### Secondary outcomes

The secondary outcomes include change in CCMS from baseline to week 64. MDS unified Parkinson’s disease rating scale (MDS-UPDRS) (38) scores comprised Part I (non-motor aspects of daily living, range 0–52, higher scores indicate greater impairment), Part II (motor aspects of daily living, range 0–52, higher scores indicate greater impairment), Part III (motor examination), Part IV (motor complications), and total score (sum of Parts I–III, range 0–236, higher scores indicate greater impairment). Purdue Pegboard Test score (PPTS) assesses fine motor skills, with two trials averaged per session. The Timed Up and Go Test (TUG) measures the time to rise, walk 3 m, and return, with two trials averaged, and records the use of assistive devices. Six-minute walk test (6MWT) (39) measures the maximum distance walked in 6 min on a flat surface, with two trials averaged, and records the use of assistive devices, which will be conducted with researcher supervision for safety. The Non-Motor Symptoms Scale (NMSS) (15), ranging from 0 to 360, evaluates domains such as sleep/fatigue, mood, and gastrointestinal function. The 39-item Parkinson’s Disease Questionnaire (PDQ-39) (40), ranging from 0 to 100, covering 8 dimensions (e.g., mobility), measures health-related quality of life. Clinical Global Impression Scale (CGI), including CGI-S (severity) and CGI-I (improvement), will be completed by a blinded assessor. LEDD will be calculated according to the standardized conversion formula proposed by Tomlinson et al. (41), recording changes from baseline at each follow-up. All secondary outcomes will be assessed at baseline; at weeks 4, 8, and 12 (during treatment); and at weeks 38 and 64 (follow-up). Among these, the NMSS, as a key secondary outcome, will be analyzed using mixed-effects models to evaluate changes in sleep/fatigue and mood domains from baseline to month 15.

#### Other outcomes

Blinding Assessment: Participants will complete a questionnaire at weeks 12 and 64 asking, “Do you believe you received true acupuncture or sham acupuncture?” with options: “yes,” “no,” or “unsure” (see Supplementary file 3). The Bang Blinding Index will be calculated to evaluate the success of blinding. This will be performed by blinded assessors unaware of group allocation (24). Treatment satisfaction: AEs, such as local pain, bruising, dizziness, or infection, will be documented at every treatment visit. Routine laboratory tests (complete blood count and liver and renal function) will be performed at baseline, week 12, and week 64 to monitor safety (15).

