**Figure 1 fig1:**
[figure not shown]
Flowchart of the study design.

**Table 1 tab1:** Study schedule for data measurements.

Assessment	Study period						
Time point	Enrolment	Baseline	Treatment phase (3 months)			Follow-up (1 year)	
	Week						
	−1	0	4	8	12	38	64
Enrolment							
Eligibility screen	**×**						
Informed consent	**×**						
Randomization		**×**					
Interventions							
TA group (*n* = 52)							
SA group (*n* = 52)							
Assessments							
CCMS		**×**	**×**	**×**	**×**	**×**	**×**
MDS-UPDRS		**×**	**×**	**×**	**×**	**×**	**×**
PPTS		**×**	**×**	**×**	**×**	**×**	**×**
TUG		**×**	**×**	**×**	**×**	**×**	**×**
6MWT		**×**	**×**	**×**	**×**	**×**	**×**
NMSS		**×**	**×**	**×**	**×**	**×**	**×**
PDQ-39		**×**	**×**	**×**	**×**	**×**	**×**
CGI		**×**	**×**	**×**	**×**	**×**	**×**
LEDD		**×**	**×**	**×**	**×**	**×**	**×**
Blinding assessment					**×**		
Treatment satisfaction					**×**		
Participants safety							
AEs			**×**	**×**	**×**	**×**	**×**
Laboratory test*		**×**			**×**		**×**

*The laboratory test includes complete blood count and differential count, absolute neutrophil count, aspartate aminotransferase, alanine aminotransferase, total bilirubin, blood urea nitrogen, creatinine, albumin, coagulation test, and 12-lead electrocardiography.

TA, true acupuncture; SA, sham acupuncture; CCMS, composite clinical motor score; MDS-UPDRS, MDS unified Parkinson’s disease rating scale; PPTS, Purdue Pegboard Test score; TUG, Timed Up and Go Test; 6MWT, 6-min walk test; NMSS, Non-Motor Symptoms Scale; PDQ-39, 39-item Parkinson’s Disease Questionnaire; CGI, Clinical Global Impression Scale; LEDD, levodopa equivalent daily dose; AEs, adverse events.

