### Statistical analysis

All statistical analyses will be conducted using SPSS version 28.0 (SPSS Inc., Chicago, IL, USA). Continuous variables will be presented as means ± standard deviations (for normally distributed data) or medians with interquartile ranges (for non-normally distributed data), determined using the Shapiro–Wilk test. Categorical variables will be expressed as counts and percentages. Between-group comparisons at baseline will be performed using independent-samples *t*-tests or Mann–Whitney *U* tests for continuous variables and chi-square tests or Fisher’s exact tests for categorical variables. Baseline covariates (e.g., age, sex, disease duration, and LEDD) will be adjusted where applicable. Longitudinal changes in primary and secondary outcomes will be analyzed using a mixed-effects model for repeated measures, with fixed effects for group, time, and group-by-time interaction, and adjusting for relevant covariates. In cases where the assumption of sphericity is violated (Mauchly’s test *p* < 0.05), the Greenhouse–Geisser correction will be applied. Post-hoc multiple comparisons will be adjusted using the Bonferroni method; sensitivity analyses will also be conducted using either unadjusted comparisons or the false discovery rate (FDR) approach. Primary analyses will follow the intention-to-treat (ITT) principle, including all randomized participants. Missing data will be handled using multiple imputation by chained equations (MICE) (24, 43), incorporating covariates (e.g., age and LEDD); sensitivity analyses will assess robustness for the 15-month follow-up. For blinding assessment, questionnaires will be administered at months 3, 12, and 15 to calculate the Bang Blinding Index, with post-hoc sensitivity analyses addressing potential biases. A per-protocol (PP) analysis will be performed on participants who complete ≥80% of scheduled treatment sessions. Exploratory subgroup analyses will examine acupuncture effects by gender, age (<60 vs. ≥60 years), and disease duration (≤1 vs. >1 year), using interaction terms in mixed-effects models to assess heterogeneity, interpreted cautiously due to power limitations. A two-tailed *p* value of < 0.05 will be considered statistically significant.

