The limitations of this study are as follows. First, differences in sensory perception (e.g., the sensation of “deqi”) may compromise blinding integrity (59); to mitigate this, blinding assessments are conducted at weeks 12 and 64, with post-hoc sensitivity analyses excluding suspected unblinded cases. Second, due to the nature of acupuncture, blinding of practitioners is not feasible, which may introduce performance bias. This risk will be minimized through standardized training and strict protocol adherence. Third, adherence may be a challenge for some patients due to the intensity of the treatment schedule (36 sessions in 12 weeks). To address this, the study team will offer transportation assistance, flexible appointment scheduling, and digital attendance tracking (e.g., WeChat check-ins) to support compliance. Finally, to ensure data homogeneity, participants with severe comorbidities or marked cognitive impairment are excluded, which may limit generalizability; future studies could expand inclusion criteria and extend follow-up durations. Additionally, while this trial compares acupuncture to sham, it does not directly contrast with standard pharmacological therapies such as levodopa for early-stage PD. Subsequent research should evaluate acupuncture’s head-to-head potential against drugs to further elucidate its role in early-stage management.

In conclusion, this study uses a rigorously designed randomized, single-blind, sham-controlled trial to evaluate the efficacy and safety of acupuncture for motor dysfunction in early-stage PD. By targeting a well-defined population, using a sensitive composite motor outcome, and standardizing the intervention, it aims to clarify the potential role of acupuncture as an adjunctive therapy to preserve motor function and reduce reliance on pharmacological treatment in the early-stage PD. Positive findings would provide a basis for integrating acupuncture into evidence-based early-stage PD care.

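### The printed blinding item cannot yield the Bang Index, its schedule conflicts across sections, and the planned exclusion of suspected unblinded cases selects on a post-randomization variable

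*Protocol article*

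**What the plan says.** **The item.** Other outcomes gives the question as "Do you believe you received true acupuncture or sham acupuncture" and the answers "with options: “yes,” “no,” or “unsure” (see Supplementary file 3". The same paragraph states: "The Bang Blinding Index will be calculated to evaluate the success of blinding".

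**The timing.**
- Table 1: the row "Blinding assessment" carries a single mark, in the week 12 column.
- Other outcomes: "Participants will complete a questionnaire at weeks 12 and 64 asking" the question.
- Discussion, limitations: "blinding assessments are conducted at weeks 12 and 64".
- Statistical analysis: "questionnaires will be administered at months 3, 12, and 15 to calculate the Bang Blinding Index".

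**The use made of the answers.** Statistical analysis mentions only post-hoc sensitivity analyses aimed at potential biases. The limitations paragraph is more specific. It names differences in needle sensation (deqi) as a threat to blinding and offers as mitigation the blinding assessments, "with post-hoc sensitivity analyses excluding suspected unblinded cases". No rule says who counts as suspected unblinded. The primary analysis is intention-to-treat and keeps everyone randomized.

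**The concern.** Acupuncturists in this trial know the allocation, so participant blinding carries much of the weight of the sham comparison. The article presents the sham device as securing that blinding and offers the questionnaire and the exclusion analysis as its checks. Three things weaken those checks.

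1. An either/or question cannot be answered yes or no. A yes names neither arm.
2. Sites cannot tell from the article when to ask. One of the stated times has no visit.
3. The guess is made after randomization and, on every stated schedule, at or after the week 12 visit where the primary endpoint is measured. A participant who feels better has a reason to guess true acupuncture whatever the needle felt like. Dropping people for guessing correctly can then remove improvers from the true arm and non-improvers from the sham arm. A robustness check built this way could make a real benefit look fragile.

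**Working it through.** **1. Item against index.** For each arm, the Bang Index is the proportion guessing correctly minus the proportion guessing wrongly, with don't-know answers in the denominator. Each reply must therefore name an arm. With the printed options only unsure can be classified. The same gap blocks any exclusion rule based on the guess.

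**2. Schedules side by side.** Months are converted as months × 52/12.

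| Place | Stated | Weeks |
|---|---|---|
| Table 1 | week 12 | 12 |
| Other outcomes; Discussion, limitations | weeks 12 and 64 | 12, 64 |
| Statistical analysis | months 3, 12, 15 | 13, 52, 65 |

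Table 1 labels the 12-week treatment phase as 3 months, and the Abstract gives follow-up to 15 months, so months 3 and 15 can fairly be read as weeks 12 and 64. Two conflicts remain. Month 12 (week 52) falls between the week 38 and week 64 visits and matches neither. It cannot mean the end of the 12-month follow-up, because that is month 15, which is listed separately. And Table 1 has no blinding mark at week 64.

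**3. Size of the possible bias.** The article gives no figure for this, so a simulation with stated assumptions is needed.

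*Input from the article:* the planning effect in Sample size calculation, 6.91 / 8.56 = 0.807, which reproduces the stated 0.81.

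*Assumptions, not from the article:*
- Improvement in SD units is d × T + N(0, 1), with T = 1 for true acupuncture and 0 for sham.
- The guess comes from a latent score b × improvement + standard logistic noise. Above 0.7 the guess is true, below −0.7 it is sham, otherwise unsure.
- Needle sensation gives nothing away.
- Every correct guesser is excluded.

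The table gives the between-group difference after exclusion (positive favours acupuncture):

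| True effect d | b = 0 | b = 0.3 | b = 0.5 | b = 1.0 |
|---|---|---|---|---|
| 0 | 0.00 | −0.20 | −0.32 | −0.60 |
| 0.50 | 0.50 | 0.29 | 0.15 | −0.18 |
| 0.81 | 0.81 | 0.60 | 0.45 | 0.08 |

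The difference among all randomized participants equals d in every cell, apart from simulation error. Averaged over arms, 33% to 44% of participants are excluded. In the d = 0 row the Bang Index is 0 in both arms at every slope, so the shift there occurs with blinding intact.

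**4. A second guess model.** Here 30% answer unsure at random, and the rest guess true with probability 1 / (1 + exp(−b × (improvement − d/2))).

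| True effect d | b = 0 | b = 0.5 | b = 1.0 |
|---|---|---|---|
| 0 | 0.00 | −0.25 | −0.45 |
| 0.81 | 0.81 | 0.55 | 0.33 |

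The direction is the same and the shifts are smaller, with 35% to 41% of each arm excluded. The size depends on the model; the mechanism does not.

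**The case against.** - **The primary result.** A reader might infer that the trial's effect estimate is biased. The article does not support this. The primary analysis includes all randomized participants, and the exclusion is a post-hoc sensitivity analysis described only in the limitations. This objection stands in full.
- **The unseen questionnaire.** A reader might also infer that the trial cannot measure blinding at all. The article points to Supplementary file 3, which may offer proper options. That limits the consequence, not the error: the options printed in the article do not fit the question printed beside them.
- **The exclusion rule.** It is undefined and appears in a sentence about needle sensation. If suspicion followed sensation and had nothing to do with outcome, the b = 0 column would apply and there would be no bias. So it would be wrong to say that the exclusion must distort the estimate. The bias is conditional.
- **The slopes and cut-points.** They have no source in the article. The only reversal to apparent harm from a real benefit in the first table needs a true effect of 0.5 SD and the steepest slope. At the article's own planning effect, the benefit shrinks but does not reverse.
- **The schedules.** Once months are translated, the conflict shrinks to month 12 and the missing week 64 mark. Data management and quality control provides monthly telephone contacts, so someone could be asked at month 12, but the article does not say that the questionnaire is given that way.

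**Conclusion.** The point holds in a limited form. Two parts rest on the text alone. The printed answers do not fit the question, so the Bang Index and any guess-based exclusion set cannot be derived from them. The schedules disagree, with month 12 unsupported and week 64 absent from Table 1. The third part is conditional. If guesses track perceived improvement and correct guessers are dropped, the sensitivity estimate moves against acupuncture even when blinding is intact. Under assumed slopes of 0.3 to 1.0 log-odds per SD, the shift is 0.20 to 0.60 SD at a null effect, and 0.81 SD falls to between 0.60 and 0.08 SD. These figures show plausible size and are not predictions. The matter should be corrected, but it does not threaten the primary analysis.

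**What to change.** 1. Change the answer options to true acupuncture, sham acupuncture or don't know, and check that Supplementary file 3 agrees.
2. State one schedule in Table 1, Other outcomes, Statistical analysis and the limitations. Weeks 12 and 64 fit the existing visits and most of the text; drop month 12. An added question at the existing week 4 visit is optional. It would record a guess before the endpoint visit, but may draw attention to allocation.
3. Report the Bang Index separately by arm with confidence intervals.
4. Replace the exclusion analysis with the full intention-to-treat estimate alongside a descriptive summary by guess. If the exclusion is kept, define the rule and label the result exploratory and subject to selection bias.

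The cost is one questionnaire item, one row of Table 1 and a few sentences. The article reports that the trial is still recruiting, so the change is practical.

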#### Sample size calculation

As no prior acupuncture studies have reported data on the CCMS, the sample size estimation was based on a randomized controlled trial of acupuncture in PD, which reported a mean change in MDS-UPDRS Part III of −2.95 ± 0.94 in the treatment group and 3.96 ± 0.94 in the control group, yielding a between-group difference (*δ*) of −6.91 and a pooled standard deviation (*σ*) of 8.56 (Cohen’s *d* = 0.81) (15). Given that the CCMS incorporates MDS-UPDRS III (40% weight) and has demonstrated higher sensitivity and lower measurement variability compared with MDS-UPDRS III alone (37), the overall detectable effect size was expected to remain comparable, even considering potential attenuation due to the use of the Park sham needle. Therefore, *δ* = −6.91 and *σ* = 8.56 were retained for sample size estimation (Cohen’s *d* = 0.81), representing a realistic yet conservative assumption for identifying clinically meaningful motor improvement in early-stage PD. Using PASS version 21.0 (NCSS LLC, Kaysville, UT, USA) for a two-sample *t*-test, with a two-sided significance level (*α*) of 0.05 and statistical power (1 − *β*) of 90%, a total of 34 participants per group was required. Considering a 20% dropout rate, common in long-term PD trials, the adjusted sample size is 43 per group. To account for inter-center variability across the two study sites, the sample size was increased by 20% (42), resulting in 52 participants per group, totaling 104 participants.

### Statistical analysis

All statistical analyses will be conducted using SPSS version 28.0 (SPSS Inc., Chicago, IL, USA). Continuous variables will be presented as means ± standard deviations (for normally distributed data) or medians with interquartile ranges (for non-normally distributed data), determined using the Shapiro–Wilk test. Categorical variables will be expressed as counts and percentages. Between-group comparisons at baseline will be performed using independent-samples *t*-tests or Mann–Whitney *U* tests for continuous variables and chi-square tests or Fisher’s exact tests for categorical variables. Baseline covariates (e.g., age, sex, disease duration, and LEDD) will be adjusted where applicable. Longitudinal changes in primary and secondary outcomes will be analyzed using a mixed-effects model for repeated measures, with fixed effects for group, time, and group-by-time interaction, and adjusting for relevant covariates. In cases where the assumption of sphericity is violated (Mauchly’s test *p* < 0.05), the Greenhouse–Geisser correction will be applied. Post-hoc multiple comparisons will be adjusted using the Bonferroni method; sensitivity analyses will also be conducted using either unadjusted comparisons or the false discovery rate (FDR) approach. Primary analyses will follow the intention-to-treat (ITT) principle, including all randomized participants. Missing data will be handled using multiple imputation by chained equations (MICE) (24, 43), incorporating covariates (e.g., age and LEDD); sensitivity analyses will assess robustness for the 15-month follow-up. For blinding assessment, questionnaires will be administered at months 3, 12, and 15 to calculate the Bang Blinding Index, with post-hoc sensitivity analyses addressing potential biases. A per-protocol (PP) analysis will be performed on participants who complete ≥80% of scheduled treatment sessions. Exploratory subgroup analyses will examine acupuncture effects by gender, age (<60 vs. ≥60 years), and disease duration (≤1 vs. >1 year), using interaction terms in mixed-effects models to assess heterogeneity, interpreted cautiously due to power limitations. A two-tailed *p* value of < 0.05 will be considered statistically significant.

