### Randomization and blinding

Participants will be randomly assigned in a 1:1 ratio to either the true acupuncture (TA) group or the sham acupuncture (SA) group using stratified block randomization by study center, with a fixed block size of four. The randomization sequence will be generated by an independent statistician using SPSS version 27.0 (IBM Corp., Armonk, NY, USA), with a predetermined random seed (seed = 20,250,504) to ensure reproducibility. Group allocations will be concealed in sequentially numbered, opaque, sealed envelopes. These envelopes will be opened by designated study coordinators only after participants have been formally enrolled.

Due to the nature of acupuncture, acupuncturists cannot be blinded. However, participants, outcome assessors, and data analysts will remain blinded throughout the study. To ensure allocation concealment and prevent potential unblinding, all treatment sessions will be conducted in separate rooms. Acupuncturists will receive standardized protocol training to minimize performance bias and to avoid any inadvertent disclosure of group assignments.

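### The primary model does not name study center or baseline CCMS; naming both would protect precision and keep the test at its nominal level, at no cost in data

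*Protocol article*

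**What the plan says.** All references are to the protocol article.

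- **Randomization and blinding:** patients are allocated 1:1 "using stratified block randomization by study center", in blocks of four, at two sites.
- **Sample size calculation:** "To account for inter-center variability across the two study sites, the sample size was increased by 20" per cent, which takes the sample from 43 to 52 per group.
- **Primary outcome:** change in CCMS from baseline to week 12, on medication. A further assessment is made "in the off-medication state (after a 12-h withdrawal from antiparkinsonian medication) at week 12".
- **Statistical analysis:** a mixed-effects model for repeated measures with group, time and group-by-time, adjusted for covariates described only as relevant. On which covariates: "Baseline covariates (e.g., age, sex, disease duration, and LEDD) will be adjusted where applicable". The sentence just before it sets out between-group significance tests at baseline.
- **Concomitant treatments:** use of permitted non-acupuncture interventions, such as rehabilitation or exercise, is recorded at each visit and entered as a covariate in the mixed model.

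No section names center or baseline CCMS as a model term. The article also does not say whether baseline CCMS enters the model as a repeated response or as a covariate.

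**The concern.** The design treats center as important twice, in the randomization and in the 20% sample allowance, yet the stated analysis does not carry it forward. Stratified randomization balances the arms within center. If center also predicts the outcome, a model without it leaves the center variation in the residual, and the reported standard error is larger than the true sampling variability of the treatment effect. The test is then conservative and some power is lost.

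Baseline CCMS is usually the strongest predictor of later CCMS. Subtracting it, as a change score does, fixes its coefficient at 1. Estimating the coefficient is never less efficient in large samples, and is clearly more efficient unless the correlation is close to 1.

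The open wording matters as well. An example list applied where applicable, next to baseline tests, leaves room to settle the covariates of the primary estimate after baseline differences have been seen.

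**Working it through.** **1. The plan's own figure.** Inputs from Sample size calculation: difference 6.91, SD 8.56, two-sided α 0.05, power 90%, two-sample t-test.

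- d = 6.91/8.56 = 0.807.
- Noncentral-t power is 0.898 at 33 per group and 0.907 at 34, which agrees with "a total of 34 participants per group was required".
- 34/(1 − 0.20) = 42.5, rounded up to 43.
- 43 × 1.2 = 51.6, rounded up to 52; total 104.

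The arithmetic reproduces, and this point does not change it.

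**2. Baseline CCMS.** Let ρ be the correlation between baseline and week-12 CCMS, with equal variances σ² at both visits. The article gives no ρ, so a range is assumed.

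- Variance of a change score: 2σ²(1 − ρ).
- Residual variance after adjusting for baseline: σ²(1 − ρ²).
- Ratio, adjusted to change score: (1 − ρ²)/(2(1 − ρ)) = (1 + ρ)/2.

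With complete data, a repeated-measures model that takes baseline as an unconstrained response and has only group, time and group-by-time gives the change-score difference as its week-12 contrast, so the ratio applies there too. Simulated ratios were 0.76, 0.86 and 0.91 at ρ = 0.5, 0.7 and 0.8, against 0.75, 0.85 and 0.90 from the formula.

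Power below uses 41 completers per group (52 × 0.8 = 41.6, rounded down). The column d = 0.5 is an assumed smaller effect.

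| ρ (assumed) | Variance ratio | n per group for 90% power, before inflation | Power, d = 0.81 | Power, d = 0.5 |
|---|---|---|---|---|
| no adjustment | 1 | 34 | 0.951 | 0.609 |
| 0.3 | 0.65 | 22 | 0.994 | 0.792 |
| 0.5 | 0.75 | 26 | 0.986 | 0.733 |
| 0.7 | 0.85 | 29 | 0.975 | 0.679 |
| 0.8 | 0.90 | 31 | 0.968 | 0.655 |
| 0.9 | 0.95 | 32 | 0.959 | 0.631 |

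**3. Center.** Let s be the share of the variance of *change* that center explains. The article gives no value, so a range is assumed. With arms balanced within center, a model without center overstates the standard error by 1/√(1 − s). The normal approximation to the true type I error is 2(1 − Φ(1.96/√(1 − s))). The simulation used 104 patients, two equal centers, blocks of four and 20,000 runs.

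| s (assumed) | SE overstated by | Type I error, formula | Simulated, center omitted | Simulated, center included |
|---|---|---|---|---|
| 0.01 | 0.5% | 0.049 | 0.050 | 0.050 |
| 0.05 | 2.6% | 0.044 | 0.043 | 0.048 |
| 0.10 | 5.4% | 0.039 | 0.040 | 0.051 |
| 0.20 | 11.8% | 0.028 | 0.030 | 0.051 |

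Power at a within-center effect of 0.5 with all 104 patients, center omitted against included: 0.69 against 0.71 (s = 0.05), 0.69 against 0.72 (0.10), 0.64 against 0.72 (0.20).

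Power at the protocol's effect, reading 8.56 as the within-center SD with 41 per group: 0.807 × √(41/2) = 3.655. At s = 0.20 the critical value becomes 1.990 × 1.118 = 2.225, and Φ(3.655 − 2.225) = Φ(1.43) = 0.92.

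**4. Level against change.** If one center scores higher by the same amount at baseline and at week 12, the shift cancels on subtraction. Simulated type I error of an unadjusted change-score test was 0.047 to 0.051 with level differences of 0.5 and 0.8 SD and ρ of 0.5 and 0.7, which is nominal. Only a difference between centers in the amount of change produces the effect in step 3.

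**The case against.** **The list is open.** The covariates are introduced as examples, and the text separately allows for relevant covariates. The article is a condensed document, and a final covariate list often sits in an analysis plan that is not shown. This stands as far as it goes: the two terms are unspecified, not excluded. It does not remove the point, because the article does state its model and covariates in two sections, and in neither does it name the factor it stratified on and enlarged the sample for.

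**Baseline is already used.** The endpoint is a change from baseline, so baseline information is not thrown away. This stands; what remains is efficiency, and at a correlation near 0.9 the gain is only about 5%.

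**Center may do no harm.** This also stands. A constant difference in level cancels, and any remaining effect is conservative.

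**Readings the document does not support:**

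- *The planned standard errors are wrong.* That depends on center staying out of the model and on centers differing in the amount of change.
- *Covariates will be picked from baseline p-values.* The tests and the adjustment are described in adjacent sentences, but nothing says that one determines the other. The wording permits such selection and does not prescribe it.
- *The off-medication result is presented as a change without a baseline.* The article never calls it a change, and a randomized post-treatment comparison is valid.

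**Conclusion.** The point holds as a low-cost improvement to the stated model, not as a threat to validity. With the named terms alone, the primary contrast gives up 10% to 25% of variance reduction at ρ of 0.8 to 0.5. Its type I error falls to about 0.043 to 0.030 if center explains 5% to 20% of the variance of change, with nothing lost if center explains about none. Both ρ and the center share are assumptions, since the article reports neither. The center figures come from a two-arm test on change with two equal centers, used as a stand-in for the week-12 contrast of the mixed model.

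The treatment estimate stays unbiased under randomization, provided the covariates are fixed in advance, and false positives are not inflated. At the protocol's d of 0.81, power stays above 90% over the ranges used here. That reassurance rests on an effect borrowed from MDS-UPDRS Part III, because no acupuncture study had reported CCMS data. If the true effect were nearer 0.5, baseline adjustment would move power from 0.609 to between 0.655 and 0.733 at ρ of 0.8 to 0.5, so the extra precision would then be worth having.

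**What to change.** State the primary model in full:

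- Response: change in CCMS at each post-baseline visit.
- Terms: group, visit, group-by-visit, center, baseline CCMS and baseline CCMS-by-visit.
- Further covariates: a closed list of age, sex, disease duration and baseline LEDD.

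Reconcile that list with the commitment under Concomitant treatments to adjust for non-acupuncture interventions: say whether that covariate belongs in the primary model or in a separate analysis. Its use is recorded at each visit, so it also needs a definition.

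Delete *e.g.* and *where applicable* from the covariate sentence, so that covariates cannot be chosen once baseline comparisons have been seen. For each secondary outcome, use that outcome's own baseline in the same way. Optionally, adjust the week-12 off-medication comparison for on-medication baseline CCMS and center.

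The cost is analysis wording only. Center and every baseline variable listed are already recorded or scheduled, and the article reports that the trial is still recruiting.
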